## Abstract

**Background:**

The denial of pregnancy is the non-recognition of the state of the current pregnancy by a pregnant woman. It lasts for a few months or for the whole pregnancy, with generally few physical transformations. In this study, we will consider the denial of pregnancy as a late declaration of pregnancy (beyond 20 weeks of gestation) as well as a lack of objective perceptions of this pregnancy. The main objective of this study is to explore the relationship between pregnancy denial and the development of the infant (attachment pattern of the infant, early interactions of mother-infant dyads, and early development of the infant).

**Methods:**

The design is a case-control prospective study, which will compare two groups of mother-infant dyads: a “case” group with maternal denials of pregnancy and a “control” group without denials of pregnancy. A total of 140 dyads (mother + infant) will be included in this study (70 cases and 70 controls) and followed for 18 months. The setting is a national recruitment setting with 10 centers distributed all over France. The follow-up of the “cases” and the “controls” will be identical and will occur over 5 visits. It will include measures of the infant attachment pattern, the quality of early mother-infant interaction and infant development.

**Discussion:**

This study aims to examine the pathogenesis of pregnancy denial as well as its consequences on early infant development and early mother-infant interaction.

**Trial registration:**

Clinical Trial Number: NCT02867579 on the date of 16 August 2016 (retrospectively registered).

## Background

### Definition of pregnancy denial

Described in the 1970s [1, 2], pregnancy denial occurs as the unconsciousness of being pregnant for several months or throughout the entire period of pregnancy. Usually, body transformations are not clearly noticeable. The prevalence of this symptom is estimated to be 1 case of denied pregnancy in 475 births [3].

There is no consensus concerning the definition of pregnancy denial. First, there is no consensus on the threshold date from when the pregnancy is considered denied if unacknowledged. On the one hand, some authors consider that the threshold date is beyond the first trimester: 14 weeks of amenorrhea [4, 5], beyond 21 weeks of amenorrhea [6] or beyond 20 weeks of pregnancy [3]. On the other hand, some authors consider a much longer duration. For example, Friedman proposed the end of the third trimester as threshold date [7]. Second, besides duration, denial may be incomplete. Two types of pregnancy denial have been proposed: partial denial with late pregnancy discovery (after 5 month of pregnancy) and total denial with pregnancy discovery while delivering [8]. Third, the encountered terminologies differ from author to another, including pregnancy denial and pregnancy negation [9]. Dayan describes pregnancy negation as “*a large range of occurrences, which are the refusal or incapacity of a pregnant woman to admit her condition”* [10]. These difficulties in properly defining pregnancy denial reflect the clinical heterogeneity of the patients.

The denial of pregnancy calls into question maternal psychological functioning. However, to date, no link between any specific psychiatric disorder and denial of pregnancy has been established [11]. During our clinical meetings, mothers who presented a denial of pregnancy report a difficult personal history with many breaks and events described as traumatic.

### Consequence of pregnancy denial

During pregnancy, a mother is getting prepared to meet her child and build quality interactions through a maturational process leading to a psychological reorganization. The pregnancy and the birth represent, for the woman, an essential phase of her psycho-affective development, comparable to the adolescence in its somatic, hormonal and psychological changes. In the past, many authors have studied these psychological reorganizations and proposed theories [12, 13]. These psychological reorganizations enable the mother to adapt to her new role and to create a containing and reassuring environment for her child. For women prone to pregnancy denial, this period of psychological reorganization is almost non-existent. The first part of the pregnancy’s story is lacking. More recently, a study found that perceiving frequent fetal movements was associated with higher scores of prenatal attachment [14]. Several publications [15–20] report observations of cases of pregnancy denial. Only one retrospective studies focused on the future of the child [21]. To our knowledge, no prospective study has focused on the future of the mother-infant relationship.

## Objectives

### Study hypothesis

We put forward the following hypothesis: an insecure attachment of the mother would participate or at least would increase the likeliness of pregnancy denial. These mothers would find it difficult (even impossible in some cases) to access the experiences of their infants, which are essential in the psychological reorganizations necessary during pregnancy to prepare the woman to accept her new functions as a mother.

Moreover, the absence or reduction of the duration of the usual 9-month period for psychological elaboration during the pregnancy calls into question its potential impact on the quality of mother-child interactions. Are there consequences on the infant’s development as well as on his pattern of attachment? We hypothesize that the attachment and the development of the infant to be born, as well as the quality of mother-infant interaction, are disturbed when the woman presents a denial of pregnancy. Specifically, we expect these consequences to be stronger with a longer duration of pregnancy denial.

### Study objectives

The primary objective of this study is to examine the relationship between pregnancy denial and infant attachment patterns, early mother-infant interaction and early infant development.

The secondary objectives of this research are as follows:To explore among women with pregnancy denial the influence of the duration period between the pregnancy announcement and delivery on infant attachment pattern, early mother-infant interaction and early infant development;To study the factors associated with pregnancy denial, including the type of maternal attachment and the existence of a maternal personality disorder and/or a psychiatric condition.

## Methods

### Trials status

This study has been retrospectively registered in the European registry (EudraCT 2011-A01498-33) and in clinicaltrials.gov (NCT02867579). The recruitments and the interventions started on April 2013 and will be completed in April 2019.

### Study design and setting

This study entitled “Attachment and pregnancy denial” is a national multicenter prospective case-control study with 13 French investigation centers (Anthony Ile-de-France, Besançon, Bordeaux, Nancy, Paris Bichat, Paris La Pitié Salpêtrière, Reims, Strasbourg, Toulouse, Amiens, Troyes, Aubagne, Lille).

### Population

*Inclusion criteria* are as follows. In the case group, dyads are composed of a woman with pregnancy denial and her infant. Pregnancy denial will be defined by a pregnancy announcement after 20 weeks of gestation and a lack of objective perceptions of the pregnancy by the woman. Women with no follow-up of the pregnancy due to geographical, social or administrative reasons (absence of insurance coverage, family conflicts, unemployment, and pregnancy hidden to the employer) will not be included. In the control group, dyads are composed of a woman without pregnancy denial and her infant. The case group and the control group will be matched on primiparous and non-primiparous mothers and on premature (birth before 37 GW) and non-premature infants.

*Exclusion criteria* are as follows: minor women (< 18 years old), women with intellectual disability, women with an acute or chronic psychotic condition, women who do not speak fluent French, women with illegal administrative status, newborn with a life-threatening prognosis, newborn with an organic malformation and/or genetic abnormality observed before leaving the hospital, and medically assisted reproduction (for the control group).

In a pragmatic way, due to the lack of data concerning the relationship between pregnancy denial and infant attachment pattern in the literature, participation will be proposed to all women with pregnancy denial during the inclusion period. Given the average number of births per year and by center (2500 on average), the number of participating centers (N=13), the frequency of pregnancy denial (2/1000 child births), the duration of the inclusion phase (48 months) and the expected participation acceptance rate (25%), 70 women with pregnancy denial will be included in this study. Therefore, 140 dyads mother-infant women will be included in this study. Based on the hypothesis of a score for disorganization [22, 23] of 3.44 ± 1.90 in the control group, inclusion of 70 dyads mother-infant per group (and evaluation of 50 dyads at 18 months because of lost of follow up) will highlight a score for disorganization of 2.37 in the case group, with a signification of 5%, a power of 90% and a bilateral (NQuery Software 7.0).

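### The printed recruitment inputs give 65 expected cases, not 70; the number of centers differs between abstract and methods; and the stated 90% power does not match the evaluable number

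*Protocol article*

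**What the plan says.** The Population section of the protocol article sets the case number by feasibility. It assumes that each center has 2500 births a year and that 25% of eligible women accept, and it lists three further inputs: "the number of participating centers (N=13), the frequency of pregnancy denial (2/1000 child births), the duration of the inclusion phase (48 months"). From these it concludes that "70 women with pregnancy denial will be included in this study", hence 140 dyads with an equal number of controls.

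The same paragraph then gives a power statement. The disorganization score is assumed to be 3.44 (SD 1.90) in controls and 2.37 in cases. The test is two-sided at 5% and power is 90%, with 70 dyads included and 50 evaluated at 18 months per group.

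Other sections bear on the inputs:
- **Study design and setting** describes a "national multicenter prospective case-control study with 13 French investigation centers" and names all 13.
- **Abstract, Methods** says: "The setting is a national recruitment setting with 10 centers distributed all over France".
- **Background, Definition of pregnancy denial** puts the prevalence at 1 in 475 births.
- **Trials status** says that recruitment and interventions "started on April 2013 and will be completed in April 2019".

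**The concern.** The five recruitment figures are presented as the reason why 70 cases will be enrolled, so a reader expects their product to be 70. It is not. One of the inputs, the number of centers, also has a different value in the abstract.

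The case number is the starting point of the sample size: the section describes the approach as pragmatic and proposes participation to every eligible woman during the inclusion period. If fewer cases are expected than stated, fewer dyads reach the 18-month assessment and power falls. A reader who wants to judge the power needs a case count, a center count and an evaluable number that agree with one another.

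**Working it through.** **Expected cases.** The formula is births per year and center × centers × frequency × years × acceptance. The inputs are from the Population section unless noted; 48 months is 4 years.

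| Variant | Calculation | Cases |
|---|---|---|
| Inputs as printed | 2500 × 13 × 0.002 × 4 × 0.25 | 65.0 |
| Prevalence from the Background | 2500 × 13 × (1/475) × 4 × 0.25 | 68.4 |
| Center count from the abstract | 2500 × 10 × 0.002 × 4 × 0.25 | 50.0 |

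The stated 70 is not reproduced. The shortfall is 5/70 = 7% as printed and 1.6/70 = 2% with 1 in 475.

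**What would give exactly 70**, changing one input at a time:
- 14 centers
- 26.9% acceptance
- 51.7 months of inclusion
- 2692 births per year and center
- a frequency of 2.15 per 1000

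Several small changes would each do it, and the document does not show which, if any, was meant.

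**Power statement.** The absolute difference is 3.44 − 2.37 = 1.07. The standardized difference is 1.07/1.90 = 0.563. Two-sided 5% two-sample t-test:

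| Analysed per group | Where it comes from | Power |
|---|---|---|
| 70 | all included dyads | 91.1% |
| 68 | smallest number reaching 90% | 90.3% |
| 65 | product as printed, no losses | 89.0% |
| 50 | the plan's evaluable number | 79.6% |
| 49 | 68.4 × 50/70 = 48.9 | 78.8% |
| 46 | 65 × 50/70 = 46.4 | 76.2% |

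The normal approximation is slightly higher and gives the same picture: 91.5% at 70, 80.4% at 50 and 77.1% at 46, with 67 per group needed for 90%. The stated 90% is thus reproduced for about 70 analysed per group, but not for the 50 the plan expects to evaluate.

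**Splitting the gap.** From 90% to 79.6% is 10.4 points, which come from attaching 90% power to 50 evaluable dyads. From 79.6% to 76.2% is a further 3.4 points, which come from the recruitment shortfall. With 1 in 475 the shortfall costs 79.6 − 78.8 = 0.8 points.

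**The case against.** The strongest defence is that this is a feasibility forecast built on rounded values. The birth figure is an average, the acceptance rate is an expectation and the frequency has one significant figure. If 2/1000 is a rounding of 1 in 475, the product is 68.4 and 70 is a fair round number. This largely stands as regards size. That 1 in 475 was the source is an inference, however, and the section prints 2/1000, so the printed derivation still needs correcting.

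Four stronger readings are tempting, but the document does not support them:

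- **That the plan will yield only 50 cases.** The derivation uses 13 centers and the design section names all 13. The 10 appears only in the abstract and never enters the calculation. It is a contradiction to remove, not evidence of a 50-case study.
- **That 70 per group has no support.** The power statement is a separate justification, and 70 analysed per group does give about 91%.
- **That the recruitment arithmetic takes power from 90% to 76%.** Most of that fall is already present at the plan's own 50 evaluable per group.
- **That the inclusion phase was really about 52 months.** April 2013 to April 2019 is 72 months. Subtracting 20 months of follow-up leaves 52, and the product would then be 70.4. But the text does not say when the last inclusion falls, and 48 + 20 = 68 months fits inside 72. There is no contradiction with 48 months.

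A reader might also note that the product has no separate term for the exclusion criteria. The 25% may already cover ineligibility, and a condensed article need not say so.

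**Conclusion.** The point holds in a limited form. The inputs as printed give 65 cases, not 70, and the abstract's 10 centers contradict the 13 given elsewhere. Both can be checked directly from the text. The recruitment gap is 7%, or 2% if 1 in 475 is used.

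Its own effect on power is modest: 3 to 4 points with 65 cases and under 1 point with about 68. The larger discrepancy in the same paragraph is that 90% power is quoted beside 50 evaluable dyads per group, where it is about 80%; 90% needs about 68 analysed per group. Taken together, 65 cases correspond to about 76% power.

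These figures assume the stated means, a common SD of 1.90, equal group sizes and 50/70 retention in both groups. The last is a simplification, because the Bias section expects more drop-out among cases.

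**What to change.** 1. State one center count in the abstract, the design section and the Population section, matching the centers that took part.
2. Either restate the expected number of cases as the product of the stated inputs (65, or about 68 if 1 in 475 replaces 2/1000), or correct the input that is wrong and show that the product then gives 70.
3. Quote power for the matching evaluable number: about 80% at 50 per group, or about 76% at 46 per group if 65 cases are expected at 50/70 retention. If 90% is kept, say that it refers to about 68 analysed per group.

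This changes wording only; design and data collection are untouched. The cost is that the stated figures become slightly less favourable.

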### Bias

We expect a percentage of women to drop out of the study before its end, especially in the case group. Mothers who experience a denial of pregnancy are more likely to drop out of the study earlier than mothers in the control group. This early attrition will impact the size of our sample.

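### The sample-size statement claims 90% power, but with 50 evaluated dyads per group its own inputs give about 80%

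*Protocol article*

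**What the plan says.** The sample-size text is in the Population section of the protocol article. It first derives 70 cases from feasibility (births, centres, frequency of denial, acceptance). It then adds a power statement:

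- The reference value is "a score for disorganization [22, 23] of 3.44 ± 1.90 in the control group".
- The design "will highlight a score for disorganization of 2.37 in the case group".
- The error rates are given as "with a signification of 5%, a power of 90% and a bilateral (NQuery Software 7.0".
- The numbers are "inclusion of 70 dyads mother-infant per group (and evaluation of 50 dyads at 18 months because of lost of follow up".

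Table 1 and the visit descriptions place the Strange Situation at the fifth visit (18 months) and at no other. The Measures section derives the continuous disorganization score from that procedure. The Bias section expects attrition and says that "Mothers who experience a denial of pregnancy are more likely to drop out of the study earlier than mothers in the control group", but gives no rate for either group.

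**The concern.** One sentence gives the difference, the SD, the significance level, the sidedness, the number included, the number evaluated and the power. These can be checked against each other, and the power does not follow from the evaluated number. A dyad lost before 18 months has no disorganization score, so 50 per group is the number that counts.

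If the true power is about 80%, the type II error for the planned difference is about 20%, twice the 10% implied. The sample size is pragmatic, so this sentence is what tells a reader how sensitive the comparison is. A reader who takes 90% at face value would give a non-significant result more weight than the design supports.

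**Working it through.** **Inputs, all from the Population section**

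- Control mean 3.44, SD 1.90; case mean 2.37.
- Two-sided 5%; stated power 90%.
- 70 included per group; 50 evaluated at 18 months, read here as per group.
- Assumption: SD 1.90 in both groups, because no case-group SD is stated.

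**Effect size**

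Difference = 3.44 − 2.37 = 1.07. Standardized difference = 1.07 / 1.90 = 0.563.

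**Trying to reproduce the stated 90% with 50 per group**

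Standard error = 1.90 × √(2/50) = 0.38. Ratio = 1.07 / 0.38 = 2.816.

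- Normal approximation: power = Φ(2.816 − 1.960) = Φ(0.856) = 80.4%.
- Noncentral t, 98 degrees of freedom: 79.6%.

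The stated 90% is missed by about 10 points.

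**With 70 per group (no loss)**

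Ratio = 1.07 / (1.90 × √(2/70)) = 3.332. Power = Φ(1.372) = 91.5% (normal), 91.1% (t).

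**Number needed per group**

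n = 2 × (1.960 + z)² / 0.563²

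- 90% (z = 1.282): 66.3, so 67 by the normal approximation and 68 by the t-test (67 gives 89.9%, 68 gives 90.3%).
- 80% (z = 0.842): 49.5, so 50 by the normal approximation and 51 by the t-test.

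Having 68 evaluable out of 70 allows a loss of 2/70 = 2.9%. The plan's own figure is 20/70 = 28.6%.

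**Detectable difference (SD 1.90)**

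| Evaluable per group | Power | Normal | t-test |
|---|---|---|---|
| 50 | 80% | 1.065 | 1.075 |
| 50 | 90% | 1.232 | 1.244 |
| 70 | 90% | 1.041 | 1.048 |

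The stated 1.07 lies between the two values for 50 per group at 80%.

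**Other readings (t-test unless noted)**

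| Reading | Power |
|---|---|
| One-sided 5%, 50 per group | 87.5% |
| Wilcoxon, 50 per group (relative efficiency 0.955) | 77.7% |
| 50 cases, 70 controls | 85.5% |
| 50 dyads in total (25 per group) | 50% |

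None reaches 90%, and the text says two-sided. At 50 per group, 90% would need an input the document does not state: a common SD of about 1.63, a case-group SD of about 1.35 or less with 1.90 in controls, or a paired analysis with a within-pair correlation of about 0.28 or more. The Population section matches groups on parity and prematurity, and the Statistical methods section lists unpaired tests.

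**Unequal retention (splits assumed; none is in the document)**

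| Cases / controls | Power (t-test) |
|---|---|
| 40 / 60 | 78.0% |
| 40 / 50 | 74.7% |
| 45 / 45 | 75.2% |
| 50 / 60 | 83.0% |

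With the total held at 100, a 40/60 split costs under 2 points against 79.6%. The 40/50 figure is low because only 90 dyads remain: an equal 45/45 split gives nearly the same power.

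**The case against.** **The case-group SD is not given.** This stands as a caveat. Power at 50 per group would be about 84% with a case-group SD of 1.70 and 87% with 1.50. But 1.90 is the only SD in the document, a common SD is the usual default, and nothing in the text supports a smaller value in cases. It is an assumption to label and does not rescue the 90%.

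**Power did not drive the sample size.** True: enrolment was fixed on feasibility, and 80% is a commonly accepted power. No estimate, test or visit changes, and a null result would be read mainly from its confidence interval. This limits the consequence, but the printed figure still does not follow from its inputs.

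**Stronger readings that the document does not support.**

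- A reader might infer that the authors forgot the loss to follow-up and computed power on 70. The stated 1.07 fits 50 per group at 80% (1.065 to 1.075) at least as well as 70 per group at 90% (about 1.05). A misprint of 90 for 80 is equally possible.
- A reader might say that 90% requires all 70 per group. About 68 suffice.
- A reader might conclude from the Bias section that power falls to 75–78%. That section gives no retention rates. If 50 describes the cases and controls are retained better, power rises above 80%.

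The direction of the stated difference (a lower score in cases, where higher means more disorganized) is a separate matter. It does not affect two-sided power.

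**Conclusion.** The point holds as a one-figure error. On the inputs printed in the Population section, 50 evaluable dyads per group give about 80% power, not 90%; the 90% would need near-complete follow-up. The conclusion rests on two readings: a common SD of 1.90, and 50 meaning per group. Reading 50 as a total makes the shortfall larger. Where the 90% came from cannot be settled from the document. The effect of differential dropout cannot be quantified without retention rates that the document does not give. The error changes how the design's sensitivity is described, not how the study is run.

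**What to change.** Restate the power sentence: with 70 dyads included and 50 evaluated per group at 18 months, the study has about 80% power (two-sided 5%, common SD of 1.90 assumed) for a difference of 1.07 points, or 90% power for a difference of about 1.24 points. State explicitly that 50 is per group and that 1.90 is applied to both groups.

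If power under unequal retention is added, give it as a range under labelled assumptions (for example 40 cases and 60 controls 78%, 40 and 50 75%, 50 and 60 83%). Do not present it as the power that follows from the Bias section.

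The cost is wording only. Enrolment, visits and assessments stay as they are; the downside is a less favourable stated power.

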### Measures

For the infants: The attachment pattern of the infant is assessed with the Strange Situation Procedure [37, 38] A mother and an 18-month-old infant are under observation in a laboratory. The observer notes the child’s reactions during 8 episodes of 3 minutes involving the separations and reunions between the mother and the child, as well as the introduction of a stranger. The situation is videotaped. The coding system of interactive behaviors allows a categorization into 4 attachment patterns: “secure”, “anxious-avoidant insecure”, “anxious-resistant insecure” and “disorganized/disoriented insecure” (regrouped into two categories: “secure” and “insecure”). Richters and associates [39] developed a method to score attachment in a continuous way. Van IJzendoorn and Kroonenberg [23] adapted and validated the algorithm for use with Strange Situation interactive scales without scores for crying. The resulting algorithm yields a continuous score for attachment that is strongly associated with the insecure vs. secure attachment classifications. Higher security scores indicate a more secure attachment relationship. Continuous scores for disorganization were derived directly from coding the conventional 9-point scale for disorganization [40], with higher scores indicating more disorganized behavior.

The quality of early mother-infant interaction is assessed with the Coding Interactive Behavior (CIB) of Feldman [31, 32]. The CIB includes 42 items (21 concerning the mother, 16 concerning the child and 5 concerning the dyad). Each item is evaluated on a 5-point scale. During the first year, 6 dimensions are extracted from the CIB items: (i) parental sensitivity, (ii) parental intrusion, (iii) infant’s social engagement, (iv) infant’s negative emotionality/infant’s engagement, (v) dyadic reciprocity and (vi) dyad’s negative states. The scale consists of 2 segmentations of 15 minutes of interactions: one session of a game and one session of feeding. The 6-month-old infant’s temperament is assessed with the French version of the Infant Characteristics Questionnaire of Bates [33]. The QT6 is a self-questionnaire administered to the mothers with 26 questions about the “difficult” temperament of the infant. It was validated in France with 794 mothers of infants aged 6 to 9 months [34].

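### The sample-size sentence states the alternative in the direction opposite to the study hypothesis: case infants at 2.37 are less disorganized than controls at 3.44

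*Protocol article*

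**What the plan says.** Three statements in the protocol article bear on this point.

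- **Methods, Population.** The planning assumption is a disorganization score "of 3.44 ± 1.90 in the control group". With "inclusion of 70 dyads mother-infant per group" and "evaluation of 50 dyads at 18 months because of lost of follow up", the study "will highlight a score for disorganization of 2.37 in the case group". The stated conditions are a two-sided 5% level and 90% power. The same section defines cases as the dyads in which the mother had a pregnancy denial, so the group labels are not ambiguous.
- **Methods, Measures.** Disorganization is a continuous score from a 9-point scale, "with higher scores indicating more disorganized behavior". A separate continuous security score is also described, on which higher is better.
- **Objectives, Study hypothesis.** Infant attachment, infant development and mother-infant interaction "are disturbed when the woman presents a denial of pregnancy", and the effect is expected to be stronger when the denial lasted longer.

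**The concern.** Read together, the three statements do not fit. The hypothesis expects worse attachment in cases. On this scale worse means a higher score, yet the case mean in the sample-size sentence is the lower of the two. Nothing in the article reverses the scale, predicts a protective effect of denial or explains a lower score in cases.

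This is the only quantified effect assumption in the article, and the Population section says that data on denial and infant attachment are lacking, so no other figure can correct it. At least one planning input must be mislabelled: the group labels, the side of 3.44 on which the case mean was placed, or the score itself. The single SD of 1.90 is attached to the 3.44 mean, so a labelling error would also put the origin of that SD in question.

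**Working it through.** **Inputs** (Population, except where noted): control mean 3.44; SD 1.90; case mean 2.37; two-sided 5%; stated power 90%; 70 included per group; 50 evaluated at 18 months, read as per group. Higher scores are worse (Measures). Two assumptions are made for the calculation: SD 1.90 in both groups and 1:1 allocation.

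**Step 1. Direction.** Case minus control = 2.37 − 3.44 = −1.07, and −1.07/1.90 = −0.56 SD. A negative sign means less disorganization in cases. The hypothesis requires a positive sign.

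**Step 2. Reproducing the stated 90%.** Power = Φ(δ / (SD × √(2/n)) − 1.960), with δ = 1.07.

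- n = 50 per group: standard error 1.90 × √(2/50) = 0.380; 1.07/0.380 = 2.816; Φ(0.856) = 80.4% (noncentral t: 79.6%).
- n = 70 per group: standard error 1.90 × √(2/70) = 0.321; 1.07/0.321 = 3.33; Φ(1.37) = 91.5% (noncentral t: 91.1%).

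The stated 90% is not reproduced with 50 per group. It is roughly reproduced only if all 70 per group are evaluated.

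**Step 3. Required numbers.** n per group = 2 × SD² × (1.960 + z)² / δ².

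- 80% power (z = 0.842): 2 × 3.61 × 7.85 / 1.145 = 49.5, so 50. Inflated for a loss of 20/70 = 28.6%, 50 / (1 − 20/70) = 70. These are the plan's own 50 and 70.
- 90% power (z = 1.282): 2 × 3.61 × 10.51 / 1.145 = 66.3, so 67 evaluable, or 67 / (1 − 20/70) = 93.8, so 94 included.

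**Step 4. Effect of correcting the sign.** Mirroring the alternative gives control 3.44 and case 3.44 + 1.07 = 4.51. Swapping the labels gives control 2.37 and case 3.44. In both, |δ| remains 1.07, so two-sided power stays at 80.4% (50 per group) and 91.5% (70 per group) with a common SD of 1.90.

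**Step 5. Difference detectable with 90% power and 50 per group.** (1.960 + 1.282) × 0.380 = 1.23. Against a control mean of 3.44, the case mean on the hypothesized side is 3.44 + 1.23 = 4.67.

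**Step 6. Sensitivity to the SD.** The documents give no second SD. As an assumption, let one group have 1.90 and the other anything from 1.4 to 2.5, with δ = 1.07 and standard error √((1.90² + SD₂²)/n). With 50 per group, power runs from about 89% (standard error 0.334) down to 67% (0.444). With 70 per group it runs from about 97% to 81%.

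**The case against.** The strongest reply is that the sign has no effect on the design. The test is two-sided, and step 4 shows that mirroring or swapping the means leaves power unchanged. Nor was N derived from this effect. The Population section sets it from expected recruitment (2500 births × 13 centers × 0.002 × 4 years × 25% = 65, given as 70), and the sentence at issue only says what that number can detect. The Statistical methods section analyses infant attachment as secure versus insecure and names no directional test of disorganization. All of this stands, and it limits the point to a wrong statement that needs correcting.

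Three stronger readings are tempting, and the documents do not support them.

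- A reader might infer that the plan leaves open which result would support the hypothesis. It does not: the Study hypothesis and Measures sections together say that higher disorganization in cases would support it.
- A reader might infer that the study is designed to show a benefit of denial. One detectable-difference sentence does not outweigh an explicit hypothesis to the contrary.
- A reader might argue that 2.37 lies so close to the bottom of the scale that a common SD of 1.90 is implausible. The article does not give the scale's lowest value, and closeness to a floor would not show that the two groups' SDs differ. Which group the SD came from is a question for the cited sources, which are not available here.

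The reply does not remove the contradiction between the three sections, and it does not make the 90% figure agree with 50 evaluable dyads per group.

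**Conclusion.** The sentence is wrong as written. The planned alternative is 1.07 points (0.56 SD) in the direction opposite to the hypothesis, and nothing in the article accounts for it. The document does not settle whether the labels are swapped, the case mean is on the wrong side of 3.44, or the figures belong to another score. On the security score, for instance, a lower mean in cases would be consistent with the hypothesis.

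Correcting the sign alone changes neither N nor power, provided that SD 1.90 applies to both groups. It would still leave the sentence wrong, because 90% power does not go with 50 evaluable per group at a difference of 1.07: the figure there is about 80%. These results assume a comparison of two means and the reading of 50 as per group. If 50 were the total (25 per group), power would be about 51%.

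**What to change.** Go back to the source figures and rewrite the sentence so that it does the following:

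1. Names the score (disorganization or security).
2. Says which group each mean and the SD come from.
3. States the alternative in the hypothesized direction.
4. Gives a power that matches the evaluable number.

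With a common SD of 1.90, two statements would be consistent: a difference of 1.07 with about 80% power at 50 evaluable per group (about 91% only if all 70 are evaluated), or 90% power at 50 per group with a detectable difference of about 1.23 (case about 4.67 against control 3.44). A case mean of 4.51, or a swap to 2.37 versus 3.44, should not be printed beside 90% power and 50 evaluable. If the SD of 1.90 turns out to belong to only one group, obtain the other and recompute.

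The cost is a check of the sources, a reworded sentence and a short recalculation. Recruitment, visits, measures and analyses need not change, unless the sponsor wants 90% power for a difference of 1.07. That would need 67 evaluable per group, or 94 included per group at the plan's implied loss of 28.6%.
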